#### Data monitoring

External trained research staff will closely monitor the progress of the trial and ensure that the trial is conducted and recorded in accordance with the study protocol via bi-weekly site visits. PHC physicians are responsible for completion of the data sets. All PHC physicians will be briefed on the data documentation protocol in the training sessions. During the study, patient CRFs will be monitored continuously and checked for completeness, implausible values and correctness. If needed, corrections or additions will be made.

### Statistical analysis

Descriptive statistics will be used to evaluate quantitative outcome measures (e.g. rates of eligibility and retention). Given an anticipated drop-out rate to follow-up of 50%, statistical analyses on ASBI effectiveness will be based on the per protocol principle (PP). Due to the pilot character of the trial, a sample size calculation will not be made. However, on the basis of previous epidemiological data [55] we assume that 4000 PHC patients will need to be screened to result in a sample size of 400 patients with an AUDIT-C score of 4 or higher for women and 5 or higher for men. We anticipate a loss-to-follow-up-rate 3 months after screening of 50%, resulting in a sample size of 200 patients (i.e. 100 per group) for data analyses. By considering a moderate intra-class coefficient (ICC between 0.05 and 0.15) between the PHC units, this sample size will be sufficient to provide statistically significant results with a medium effect size (d between 0.4 and 0.6) for the analyses of the primary and secondary effectiveness endpoints. Paired *t* tests will be used for pre-post-comparison of drinking outcomes based on AUDIT-C score between baseline and follow-up within the groups. The qualitative data on the implementation processes and potential future maintenance will be summarized for a narrative analysis.

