## Methods/design

### Aim

The primary aim of this study is to assess the feasibility of a proposed fully cluster randomised controlled trial of the effectiveness of ASBI in primary health care in Kazakhstan. The secondary aim is to explore the feasibility and acceptability of implementing ASBI in this setting from the perspective of patients and physicians.

Specific objectives are as follows:
To conduct a two-arm pilot feasibility cluster randomised controlled trial (cRCT) (with randomization at the level of PHCU) to assess the feasibility of a future definitive cRCT of ASBI in primary care in Kazakhstan;To explore the feasibility and acceptability of ASBI and trial processes to physicians and patients;To identify key determinants of ASBI implementation from the perspective of physicians and patients to identify specific facilitators and barriers to ASBI delivery in PHC;To estimate the parameters for the design of a definitive cRCT of ASBI in primary care in Kazahkstan, including rates of eligibility, consent, participation and retention.

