### Design

This pilot trial will use a two-arm cluster randomised design with embedded qualitative process evaluation to explore feasibility and acceptability in six PHC units (PHCU) in Kazakhstan. Stratified randomization with computer-generated random numbers will be used to allocate three PHCUs to the intervention and three PHCUs to the control group, with stratification based on an initial baseline assessment of the mean number of patient visits per PHCU per day.

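### The plan assumes clustering between PHCUs, but its only named effectiveness test, a within-group paired t test, ignores clustering and makes no comparison between the randomised arms

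*Protocol article*

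**What the plan says.** The Design section randomises six PHCUs and will "allocate three PHCUs to the intervention and three PHCUs to the control group". Table 1 gives the effectiveness measure as change in AUDIT-C from baseline to follow-up among patients with risky, hazardous or harmful drinking.

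The Statistical analysis section makes no formal sample size calculation. It expects that "4000 PHC patients will need to be screened to result in a sample size of 400 patients" above the AUDIT-C cut-off, assumes 50% loss to follow-up, and continues: "resulting in a sample size of 200 patients (i.e. 100 per group) for data analyses". It then brings in clustering ("By considering a moderate intra-class coefficient (ICC between 0.05 and 0.15) between the PHC units") and concludes that this number is enough for statistical significance at d between 0.4 and 0.6 on the primary and secondary effectiveness endpoints.

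The next sentence names the test: paired t tests comparing baseline with follow-up AUDIT-C within each group. The article names no other effectiveness test, no term for PHCU and no comparison between arms.

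**The concern.** Two adjacent sentences do not fit together. The first accepts that patients of the same PHCU resemble one another and uses this to judge the sample size. The second names a test whose standard error is right only if the change scores are independent. If change scores cluster, that standard error is too small and p-values and intervals look more certain than three PHCUs per arm allow.

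The test also sets the randomisation aside. A change within the intervention arm can arise without any effect of the brief intervention. Control patients also receive feedback and a leaflet, and the analysed patients were selected for a high baseline score, so some fall is expected in both arms through regression to the mean. Setting one within-arm p-value beside the other does not test the difference between arms.

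At stake is whether the pilot's effectiveness signal, which will inform a decision about a definitive trial, is reported with far too much confidence.

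**Working it through.** **Inputs from the article**
- 4000 screened, 400 above the cut-off, 50% lost to follow-up (Statistical analysis).
- Six PHCUs, three per arm (Design).
- ICC 0.05 to 0.15; d 0.4 to 0.6 (Statistical analysis).

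**Assumptions**
- Equal PHCU sizes, two-sided 5% unless stated, 80% power where a power is needed. The article gives no alpha, sidedness or power.

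**1. The plan's headcount.** 400 × (1 − 0.50) = 200, or 100 per arm, which reproduces. Mean patients per PHCU: m = 100/3 = 33.3.

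**2. Design effect.** DE = 1 + (m − 1) × ICC.
- ICC 0.05: 1 + 32.3 × 0.05 = 2.62; effective n per arm 100/2.62 = 38
- ICC 0.10: 4.23; effective n 24
- ICC 0.15: 5.85; effective n 17

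**3. The sufficiency statement.** It cannot be reproduced with certainty because alpha, sidedness and power are missing.
- Two arms: detectable d = (1.960 + 0.842) × √(2 × DE/100) = 0.64 (ICC 0.05) to 0.96 (ICC 0.15). This does not match.
- One group of 100, one-sided 5%: (1.645 + 0.842) × √(DE/100) = 0.40 to 0.60. This matches, but it is a detectable change within one arm. Whether the authors computed it this way is unknown.

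**4. False-positive rate of the named test, if change scores have the stated ICC.** The true variance of the mean change is DE times what the test assumes, so the rate is 2 × [1 − Φ(c/√DE)].

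| ICC | √DE | rate, c = 1.960 | rate, c = 1.984 (t, 99 df) |
|---|---|---|---|
| 0.05 | 1.62 | 22.6% | 22.0% |
| 0.10 | 2.06 | 34.1% | 33.5% |
| 0.15 | 2.42 | 41.8% | 41.2% |

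Simulation (40,000 trials; PHCUs of 33, 33 and 34) gave 22.5% at ICC 0.05 and 43.3% at ICC 0.15.

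**5. The same test if PHCUs differ only by a stable level.** A PHCU effect that is equal at baseline and follow-up drops out of each patient's difference. Simulation gave 4.9% to 5.1%.

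**6. Between the two.** A change-score ICC of only 0.02, chosen for illustration, gives DE = 1.65 and a rate of 12% to 13%.

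**7. Why two within-arm tests do not replace a comparison.** Suppose both arms change by the same 0.2 SD, with no clustering. Each test has power Φ(0.2 × √100 − 1.96) = Φ(0.04) = 0.516. The pattern of a significant intervention arm and a non-significant control arm then occurs with probability 0.516 × 0.484 = 0.25, although the arms do not differ.

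**8. Power of a between-arm test on six PHCU means.** Noncentrality = d/√(2 × DE/100); critical value 2.776 on 4 df.
- ICC 0.05: noncentrality 1.75 (d 0.4) and 2.62 (d 0.6); power 27% and 51%
- ICC 0.15: noncentrality 1.17 and 1.75; power 15% and 27%

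These take d and the ICC on the scale of the analysed outcome.

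**The case against.** **The inflation is conditional.** A reader might infer that the plan has a 22% to 42% false-positive rate outright. The article does not support that, because it never says whether the ICC refers to AUDIT-C level or to change, and step 5 shows that a purely stable level effect leaves the test at 5%. This objection stands and sets the lower end of the range. Perfect stability is nevertheless the favourable extreme. PHCU physicians trained for the study deliver the intervention and complete the forms, so differences in delivery between PHCUs would appear in the change scores. The article also applies its ICC to effectiveness endpoints, and Table 1 defines effectiveness as change.

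**The null is narrow.** A reader might take these rates as the chance of a false intervention effect. They are not. They concern no pre-post change within one arm, and no between-arm test is named to which they could apply.

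**Feasibility rates.** A reader might extend the point to recruitment and retention: that they will be pooled, reported too precisely, and leave the definitive trial without an ICC. The documents do not support this. The article says only "Descriptive statistics will be used to evaluate quantitative outcome measures (e.g. rates of eligibility and retention" and similar measures), which allows reporting by PHCU and plans no interval. It gives no ICC for retention. The fourth objective ("To estimate the parameters for the design of a definitive cRCT of ASBI in primary care") lists its rates after the word including, so the list is open. Intervals by PHCU and ICC estimation are commonly left to an analysis plan that is not shown.

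**Weight.** This is a pilot whose key outcomes are recruitment and retention, and AUDIT-C change is one RE-AIM domain. That limits the importance of the point. It does not remove it, because the article itself claims that the sample suffices for significant effectiveness results.

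**Conclusion.** The point holds as an inconsistency in what the Statistical analysis section states. A between-PHCU ICC is assumed for the effectiveness endpoints, and the only test named then ignores it and makes no use of the randomised comparison.

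The false-positive rate of the nominal 5% within-arm test lies between about 5% and about 42%. The lower end requires PHCU effects that are perfectly stable over three months. The range of about 22% to 42% requires AUDIT-C change itself to have an ICC of 0.05 to 0.15, with equal PHCUs of about 33 patients. The article does not settle which applies.

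The point should be corrected before analysis, but it does not undermine the feasibility aims.

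**What to change.** - Replace the paired t tests with one between-arm comparison of follow-up AUDIT-C that respects the PHCU as the unit of randomisation. Use either a t test on six baseline-adjusted PHCU means (4 df) or a mixed model with a PHCU random effect and a small-sample correction such as Kenward-Roger.
- Report within-arm change descriptively.
- Present the result as an estimate with a 95% interval, and not as a significance verdict.
- State which variable the ICC of 0.05 to 0.15 refers to.
- Withdraw the statement that 200 patients are sufficient, or confine it to the quantity and error rates for which it was worked out.

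No new data are needed, but this is more than a change of wording, because the analysis then answers a different question: the difference between arms. Intervals will be wide, and power on 4 df is only about 15% to 51% at d 0.4 to 0.6 (two-sided 5%). That is an honest reflection of six PHCUs.

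Reporting the estimated ICC, and the feasibility rates per PHCU with intervals, would be a useful optional addition for planning the definitive trial. Its absence is not an error in the article.

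### The statement that 200 analysed patients in six PHCUs suffice for significance at d = 0.4 to 0.6 with an ICC of 0.05 to 0.15 does not follow from the design

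*Protocol article*

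**What the plan says.** The Design section says that stratified randomisation will "allocate three PHCUs to the intervention and three PHCUs to the control group". The Statistical analysis section declines a sample size calculation because the trial is a pilot. It then gives a chain of numbers. First, "we assume that 4000 PHC patients will need to be screened to result in a sample size of 400 patients" above the AUDIT-C cut-offs. A 50% loss by three months follows, "resulting in a sample size of 200 patients (i.e. 100 per group) for data analyses". Finally, allowing for a "moderate intra-class coefficient (ICC between 0.05 and 0.15) between the PHC units", it concludes that "this sample size will be sufficient to provide statistically significant results with a medium effect size (d between 0.4 and 0.6") in the effectiveness analyses.

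Alpha, sidedness and target power are not stated. The only effectiveness test named is a paired t test of AUDIT-C from baseline to follow-up within each group. No between-arm test is named.

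**The concern.** The section declines a calculation and then asserts what such a calculation would have shown. The assertion expressly takes clustering into account, yet 100 per group is the number that an individually randomised comparison needs for 80% power at d = 0.4. With only six clusters and ICCs of this size, that number cannot carry over.

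Two misreadings are possible. A non-significant AUDIT-C result could be taken as evidence against a medium effect. Whoever designs the definitive cluster trial, for which this pilot is meant to supply parameters, could take three clusters per arm to be adequate.

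**Working it through.** **Inputs from the protocol article.** 200 analysed, 100 per arm (Statistical analysis); three PHCUs per arm (Design); ICC 0.05 to 0.15 and d 0.4 to 0.6 (Statistical analysis). Mean cluster size m = 200/6 = 33.3.

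**Assumptions, not in the article.** Two-sided alpha 0.05; 80% power as the usual minimum for a sample to be called sufficient; equal cluster sizes; an unadjusted comparison of the arms at follow-up.

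**Step 1: the plan's own numbers.** 400 × 0.5 = 200, which is correct. Without clustering, SE(d) = √(2/100) = 0.141. A two-sample t test with 100 per arm then has 80.4% power at d = 0.4, 94% at 0.5 and 99% at 0.6. So 100 per group matches an unclustered calculation at the lower end of the stated effect range.

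**Step 2: design effect.** DE = 1 + (m − 1) × ICC; effective n per arm = 100/DE; SE(d) = √(2 × DE/100).

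- ICC 0.05: DE = 1 + 32.3 × 0.05 = 2.62; effective n = 38; SE = 0.229
- ICC 0.10: DE = 4.23; effective n = 24; SE = 0.291
- ICC 0.15: DE = 5.85; effective n = 17; SE = 0.342

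**Step 3: between-arm power.** Comparing three with three cluster means leaves 2 × (3 − 1) = 4 degrees of freedom, so power comes from the noncentral t distribution with noncentrality d/SE. The normal approximation, Φ(d/SE − 1.96), treats the variance as known and is too lenient for six clusters.

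| ICC | Method | d = 0.4 | d = 0.5 | d = 0.6 | Smallest d with 80% power |
|---|---|---|---|---|---|
| 0.05 | t, 4 df | 27% | 39% | 51% | 0.86 |
| 0.05 | normal | 42% | 59% | 75% | 0.64 |
| 0.10 | t, 4 df | 19% | 26% | 35% | 1.09 |
| 0.10 | normal | 28% | 40% | 54% | 0.82 |
| 0.15 | t, 4 df | 15% | 21% | 27% | 1.29 |
| 0.15 | normal | 21% | 31% | 42% | 0.96 |

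Simulated cluster-level t tests (200,000 runs each) at the four extreme combinations gave 27.2%, 51.4%, 14.9% and 27.1%, in agreement with the 4-df values.

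**Step 4: precision.** With 4 df the critical value is 2.776. The expected 95% half-width is 2.776 × 0.229 = 0.64 SD at ICC 0.05 and 2.776 × 0.342 = 0.95 SD at ICC 0.15.

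**Step 5: other readings that keep the clustering.**

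- One-sided alpha 0.05, normal approximation: 84% at ICC 0.05 and d = 0.6, but 32% at ICC 0.15 and d = 0.4.
- Baseline adjustment with an assumed correlation of 0.5 (variance × (1 − 0.5²)): at ICC 0.05 and d = 0.6, 86% by normal approximation and 63% with 4 df; at ICC 0.15 and d = 0.4, 27% and 18%.
- Baseline adjustment with an assumed correlation of 0.7: at the same two combinations, 96% and 78%, then 37% and 24%.
- Within-group paired test, n = 100, same design effect, d on the scale of the SD of change: 38 to 96% by normal approximation, passing 80% at ICC 0.05 for d = 0.5 and 0.6 (87% and 96%) and at ICC 0.10 for d = 0.6 (83%). With 2 df for three clusters it is 17 to 51%. With clustering ignored it is 98% at d = 0.4.

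**The case against.** The strongest objection is that this is a pilot. Its key outcomes are recruitment and retention, analysed descriptively, and effectiveness is one RE-AIM domain among five. No recruitment target or patient's care turns on the sentence. That stands, and it lowers the weight of the point. It does not make the statement correct.

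A second objection is that the calculation above analyses a test that the article does not name. The named test is paired and within group, and ignoring clustering it has ample power. Stable differences between PHCUs also cancel in a pre-post change, so the ICC of change could be lower than the stated range; the paired figures above are therefore driven by assumption. But the sentence itself invokes the stated ICC, and a within-group change is not the comparison that was randomised.

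Three stronger readings may tempt a reader, and the documents support none of them.

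- *80% power is reachable only by ignoring clustering.* Step 5 shows combinations above 80% with clustering kept, mainly at ICC 0.05 and d = 0.5 to 0.6.
- *With six PHCUs no number of patients could give 80% power, even at d = 0.6 and ICC 0.05.* With unlimited patients per PHCU, SE = √(2 × 0.05/3) = 0.183. Power is then 69% for an unadjusted test on 4 df but 91% by normal approximation, so this depends on the analysis.
- *The authors must have used an unclustered formula.* The number matches one, but the article shows no calculation, so its origin is unknown.

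**Conclusion.** The sufficiency statement is wrong as written. Under two-sided alpha 0.05 and an unadjusted between-arm comparison, power over the article's own ranges is about 15 to 51% (4 df) or 21 to 75% (normal approximation). The smallest effect with 80% power is d = 0.86 to 1.29 or d = 0.64 to 0.96 respectively, in every case above the stated 0.4 to 0.6. More favourable unstated assumptions lift some combinations past 80%, but none of the variants examined that apply the stated ICC holds over the whole range. The two power ranges should be read together, because the article fixes neither the test nor its degrees of freedom.

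This is not a finding that the pilot is too small. Severity: should be fixed, since the key outcomes are feasibility rates.

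**What to change.** Delete the sufficiency sentence. State instead that the effectiveness analysis is exploratory and is reported as an estimate with a 95% confidence interval that allows for clustering by PHCU.

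If a figure is to be kept, give either the power range or the expected half-width (about 0.64 to 0.95 SD with 4 df), together with its assumptions: two-sided 0.05, unadjusted, three PHCUs per arm, about 33 analysed patients per PHCU, ICC 0.05 to 0.15.

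The cost is a few sentences of wording. No extra patients or PHCUs are needed, and trial conduct does not change. The only drawback is that the stated figure becomes less favourable.

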**Methods:**

Six primary health care units in the region of Pavlodar will be cluster randomised to either an intervention (WHO manualised 5 min alcohol brief intervention plus alcohol leaflet) or control group (simple feedback plus alcohol leaflet). Primary feasibility measures will be rates of participation at baseline and retention of eligible patients at the 3-month follow-up point. Patient/physician questionnaires and physician focus groups will assess additional dimensions of feasibility, as well as acceptability, according to the RE-AIM framework: Reach (rates of eligible patients screened/received advice); Effectiveness (change in AUDIT-C score); Adoption (rate/representativeness of participating physicians); Implementation (quality of ASBI/barriers and facilitators to delivery); and Maintenance (potential sustainability of intervention).

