#### Follow-up assessments

At the end of the recruitment period, participating physicians will be asked to provide their views on the implementation and potential maintenance of ASBI using structured questionnaires which will be administered by local research staff. The outcomes will inform qualitative focus groups (Table 1), which willl last approximately 60 to 90 min and will be moderated by an experienced researcher from the national study team. A semi-structured topic guide will be developed to focus discussions, drawing on key themes emerging from the structured questionnaire findings and the three major areas of interest—quality and consistency of ASBI delivered, barriers/facilitators to implementation of ASBI in PHC and the long-term sustainability of ASBI in this setting.

**Table 1 Tab1:** Key outcome measures including domains of the RE-AIM framework [54]

Dimension	Outcome measures	Assessment tool and evaluation method
Feasibility	- *Rate of eligibility*: percentage of eligible participants recruited	Case-report form; descriptive statistics
	- *Participation and retention at 3 months follow-up*: percentage of enrolled participants retained at 3 months	
Reach	- *Proportion of patients screened at baseline* Numerator: Total number of completed screens Denominator: Total number of all patients eligible for screening	
	- *Proportion of consulting patients intervened at baseline* Numerator: Total number of screen-positive patients receiving advice Denominator: Total number of patients screened positive	
Effectiveness	- *Change in AUDIT-C* score between baseline and follow-up amongst patients with risky, hazardous or harmful drinking	
Adoption	- *Proportion of staff invited that participated* Numerator: Total number of participating physicians Denominator: Total number of primary care physicians invited	
	- *Description and representativeness of staff who delivered* the screening and advice (PHC provider level)	
Implementation	- *Quality and consistency of the delivery of ASBI* given (PHC provider level; patient level) measured by quantitative interviews, provider focus groups	Provider questionnaire; provider focus groups; descriptive statistics and qualitative data analyses (content and narrative analyses)
	- *Implementation determinants* (barriers, facilitators) of ASBI delivery (PHC provider, Patient level) collected by quantitative interviews, provider focus groups	

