#### Study outcome measures

The key outcome measures to assess feasibility will be the percentage of eligible patients recruited to the study at baseline and the retention rate of eligible patients at 3-month follow-up. Additional outcome measures to assess the feasibility and acceptability of implementing ASBI in primary care in Kazakhstan will be based on Glasgow’s RE-AIM framework for evaluating public health interventions [54]. RE-AIM consists of five dimensions (**R**each, **E**ffectiveness, **A**doption, **I**mplementation and **M**aintenance), which can be measured at the individual (patient/provider) or organisational (clinic/practice) level to help to determine the potential impact of an intervention.

Outcome measures relating to feasibility and each domain of the RE-AIM framework are detailed in Table 1.

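### The Statistical analysis section promises significant results on primary and secondary effectiveness endpoints that are defined nowhere and do not fit the trial's feasibility outcomes

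*Protocol article*

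**What the plan says.** The article sets out its hierarchy in several places.

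- **Aim:** "The primary aim of this study is to assess the feasibility of a proposed fully cluster randomised controlled trial". None of the four specific objectives is to show effectiveness.
- **Abstract, Methods:** "Primary feasibility measures will be rates of participation at baseline and retention of eligible patients at the 3-month follow-up point". Effectiveness appears afterwards, as one of the five RE-AIM dimensions, and is equated with change in AUDIT-C score.
- **Study outcome measures:** "The key outcome measures to assess feasibility will be the percentage of eligible patients recruited to the study at baseline", together with 3-month retention. The RE-AIM outcomes are described as additional.
- **Table 1, Effectiveness row:** one entry, the change in AUDIT-C "score between baseline and follow-up amongst patients with risky, hazardous or harmful drinking".

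The Statistical analysis section says that no sample size calculation will be made because this is a pilot. It then says of the expected 200 analysed patients that "this sample size will be sufficient to provide statistically significant results with a medium effect size (d between 0.4 and 0.6"), and ends that sentence with "for the analyses of the primary and secondary effectiveness endpoints". The only test it names is a paired t test for "pre-post-comparison of drinking outcomes based on AUDIT-C score between baseline and follow-up within the groups".

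**The concern.** A trial whose primary outcomes are feasibility rates should not also have a primary effectiveness endpoint for which significance is promised, least of all one that is never named. A reader of the Statistical analysis section alone would take this to be an effectiveness trial with at least two effectiveness endpoints. A reader of the Aim, the Study outcome measures and Table 1 would take it to be a feasibility trial with one supporting effectiveness measure. Both readings cannot be right.

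What is at stake is how the pilot is reported. If an AUDIT-C comparison reaches significance, this sentence gives grounds for calling it a result on a primary effectiveness endpoint, and that could colour the decision on the definitive trial. If it does not, the same sentence makes the pilot look like a negative effectiveness study, which it was not designed to be.

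**Working it through.** **1. The plan's own figure.** The Statistical analysis section assumes 4000 patients screened and 400 positive, which is 400 / 4000 = 10%. With 50% loss to follow-up, 400 × (1 − 0.50) = 200 patients are analysed, or 200 / 2 = 100 per group. The headcount reproduces. No alpha, sidedness or power is attached to the statement that it is sufficient. Whether 100 per group really supports that statement at the quoted intra-class coefficient is a separate question, and nothing below depends on it.

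**2. The passages side by side.**

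| Place | Primary or key outcome | Effectiveness |
|---|---|---|
| Aim | Feasibility of a definitive trial | Not an objective of the pilot |
| Abstract, Methods | Participation and retention | Change in AUDIT-C, one RE-AIM dimension |
| Study outcome measures | Recruitment and retention | One of the additional RE-AIM outcomes |
| Table 1 | Recruitment and retention, under Feasibility | One measure: change in AUDIT-C |
| Statistical analysis | Refers to a primary effectiveness endpoint, not named | Also refers to secondary effectiveness endpoints, not named |

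The last row does not fit the four above it. One listed measure cannot supply both a primary and a secondary endpoint.

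**3. Can the missing endpoints be recovered from the data plan?** The section on Baseline assessments lists what is collected at 3 months: AUDIT-C, the physician's impression of drinking, and patients' views and acceptance. The full AUDIT is listed at baseline only. AUDIT-C is thus the only drinking score at follow-up, and nothing collected is labelled a secondary effectiveness endpoint.

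**4. Size, from the tests actually named.** The only test named is the paired t test on AUDIT-C within groups. Taken as one test per arm, this gives k = 2. Assume two-sided 5% per test (the article states no alpha), independent arms, and no true change in either arm:

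P(at least one false positive) = 1 − (1 − 0.05)^k = 1 − 0.95² = 1 − 0.9025 = 0.0975, about 9.8%.

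The excess over 5% comes from testing each arm separately. A single between-arm test of the one listed measure would stay at 5%.

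**5. Illustrations only.** If there were two endpoints, each tested in both arms, then k = 4 and 1 − 0.95⁴ = 0.1855. A simulation with correlated endpoints gives about 17% at correlation 0.5 and 15% at 0.8. With one between-arm test for each of two endpoints, the figure is 9.0% at correlation 0.5 (range 7.8% to 9.7%). The article supplies no endpoint count, so these show what could follow and do not measure this plan.

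**The case against.** The strongest reply is that this is a stray phrase in a condensed article. The effectiveness outcome is in fact fixed: one score, one population, one follow-up time. The section stresses the pilot character, and the Background and Discussion speak only of potential impact and potential effectiveness. *Primary effectiveness endpoint* could mean primary within the effectiveness domain, leaving feasibility first overall.

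Much of this stands, and it rules out several stronger readings that a reader might infer:

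- *That the choice of AUDIT-C outcome is left open.* The Abstract and Table 1 fix it. Single items, or the proportion below the cut-off, appear nowhere as outcomes.
- *That a large family of tests is planned.* The plural in the paired t test sentence does not establish that. Family-wise figures above 9.75% rest on an assumed endpoint count.
- *That the result will be presented as confirmatory.* The article never uses the word. The sentence is a statement about adequacy of sample size, so this is a risk and not a stated intention.
- *That Table 1 prescribes description only, so any test contradicts it.* The entry "Case-report form; descriptive statistics" stands in the first Feasibility row. Carrying it down to Effectiveness assumes a merged cell, which the extracted text cannot confirm.
- *That the lack of an alpha split is itself an error.* That may sit in an analysis plan not shown here.

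The reply does not remove the contradiction. Even on the within-domain reading, a primary and a secondary endpoint need at least two measures, and only one is listed. A separate analysis plan could define more endpoints, but it would not reconcile a promise of significance for them with the feasibility aim printed here.

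**Conclusion.** The point holds as a contradiction in what the article states. The Statistical analysis section claims sufficiency for significant results on effectiveness endpoints that are undefined and out of line with an outcome hierarchy in which recruitment and retention come first and change in AUDIT-C is the sole effectiveness measure. This conclusion needs no numerical assumption.

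The only error rate tied to the text is 9.75%. It assumes two-sided 5% for each of two independent within-arm tests and no change over time in either arm. The weight is moderate: feasibility outcomes and patient numbers are unaffected, and the harm lies in how an AUDIT-C result might be presented and carried into the definitive trial.

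**What to change.** In the Statistical analysis section:

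1. Delete the statement that the sample will suffice for statistically significant results on primary and secondary effectiveness endpoints.
2. State that recruitment at baseline and retention at 3 months are the only primary outcomes.
3. State that change in AUDIT-C at 3 months among risky, hazardous or harmful drinkers, as listed in Table 1, is the single exploratory effectiveness outcome. Report it as one between-arm estimate with a 95% confidence interval and no claim of effectiveness.
4. Bring the sentence on within-group paired t tests into line, so that those comparisons do not carry the effectiveness statement.

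The cost is wording only. AUDIT-C is already collected at both times, so no patients, visits or data are added. The downside is that the pilot gives up a significance-based effectiveness statement.
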